## Abstract

**Background:**

Migraine is common in childhood, peaks in adolescents and persists into adulthood in at least 40% of patients. There is need for early interventions to improve the burden of disease and, if possible, reduce chronification. The aim of the project is to compare two types of ambulatory treatment strategies regarding their effect on headache days and quality of life in 6 to 11 year old children with migraine: 1) the routine care in pediatricians’ practices (intervention group A) and 2) a structured interdisciplinary multimodal intervention administered at social pediatric centers (intervention group B).

**Methods:**

The study is a nation-wide cluster-randomized study. Based on the postal codes the regions are randomly assigned to the two intervention-strategies. Children with migraine are recruited in the pediatric practices, as common outpatient-care in the German health-care system. Parents rate headache frequency, intensity and acute medication intake at a daily basis via a digital smartphone application specifically designed for the study. Migraine-related disability and quality of life are assessed every 3 months. Study duration is 9 months for every participant: 3 months of baseline at the pediatric practice (both groups); 3 months of intervention at the pediatric practice (intervention group A) or at the social pediatric center (intervention group B), respectively; 3 months of follow-up at the pediatric practice (both groups).

**Discussion:**

Results of the planned comparison of routine care in pediatric practices and interdisciplinary social pediatric centers will be relevant for treatment of children with migraine, both for the individual and for the health care system.

**Trial registration:**

The study was approved by the ethics committee at the Ludwig-Maximilians-University Munich (number 18–804) and was retrospectively registered on 27 April 2021 in the WHO approved German Clinical Trials Register (number DRKS00016698).

## Background

Migraine is a chronic disease often starting in childhood. The Barmer health insurance company dataset, which is covering 11% of all German policyholders, showed that in 2015 approximately 1% of all children received a diagnosis of migraine already at the age of primary school (6 to 11 years of age) [1]. In patients with migraine diagnosed at the age of 7 years, migraine persists into adulthood in 65% of the affected females and 21% of the affected males [2].

The Barmer insurance data also reveal that only half of the primary school children diagnosed with migraine got appropriate medication e.g. NSAID, but 2.1% were at least once in inpatient treatment for migraine. Only 6% of the affected children received an interdisciplinary therapy at a social pediatric center (unpublished data). Social pediatric centers are regional neuropediatric centers offering interdisciplinary treatment for children with chronic diseases. They belong to the customary care institutions in Germany.

It has repeatedly been shown that interdisciplinary treatment is effective in adult patients with migraine: e.g., in one study 42.5% of patients achieved a reduction of headache days of more than 50% even in the long term [3] and in another study, the number of headache days was significantly reduced from 13.8 ± 7.6 to 8.2 ± 6.2 [4]. Comparisons with standard basic care have shown superiority of multimodal treatment [5, 6].

Studies about the efficacy of multimodal treatment in young children with migraine do not exist so far. Children with migraine have a shorter migraine history and less comorbidities, such as other pain syndromes or psychiatric disorders, than adult migraine patients. Therefore, an early interdisciplinary multimodal treatment in young children may lead to an even better outcome in comparison to adults and may prevent the establishing of co-morbidities in the long term. Effective elements of treatment seem to include counselling on life style factors [7, 8] and psychotherapeutic [9] and physiotherapeutic measures [9, 10]. These interdisciplinary multimodal approaches are a distinguishing feature of German social pediatric centers.

Therefore, we designed an interdisciplinary multimodal intervention for treatment of pediatric migraine in social pediatric centers and a randomized controlled study to evaluate its effectiveness compared with standard basic pediatric care over a 9 months interval (elements of the interdisciplinary intervention: see 2.3. Study Design).

The aim of the presented study is to evaluate if an early intervention in young children at the time migraine has just started leads to a reduction of headache days and headache intensity as well as to a lower intake of analgesics and to an amelioration of quality of life.

## Methods/design

### Patient involvement

Children with migraine are treated in pediatric practices and social pediatric centers in Germany. As interdisciplinary multimodal treatment showed superior effects in the care of adults with migraine, we included pediatric, psychological and physiotherapeutic modules in the treatment of children with migraine in our clinical work at the social pediatric center in Munich. The satisfaction with this treatment of both children with migraine and their parents thereby ameliorated in a significant way. Based on this experience, we developed the patient-centered, structured, interdisciplinary multimodal intervention “moma – modules on migraine activity”, presented in this protocol. Nevertheless, pediatricians in practice are the standard basic pediatric care for children with migraine in Germany and are often very effective. Thus, we chose treatment in pediatric practices as comparative intervention strategy in our study design. Another aspect of patient involvement in the study design was that, to our clinical experience, the acceptance of treatment support via digital applications is high among parents in the neuropediatric field. Therefore, we developed the “moma app” for smartphones to facilitate the documentation of headache symptoms for the parents of participating children with migraine. The results of the study will be disseminated not only in scientific journals but also in public media to attain transparency for patients and their parents about the effectiveness of different treatment strategies for children with migraine.

### Selection of sample

Children between 6 and 11 years of age with migraine with a statutory health insurance (approx. 90% of the population) and whose parents consent to participation are eligible for the study. Children are recruited by their pediatricians in practice. The pediatrician diagnoses migraine according to the International Classification of Headache Disorders 3rd edition (ICHD-3) [11], with the help of a standardized, electronic migraine checklist that was developed for the study.

Inclusion criteria are as follows:
Age 6 to 11 yearsDiagnosis of migraine (according to the International Classification of Diseases ICD-10, classification numbers G43.x), based on the International Classification of Headache Disorders (ICHD-3) [11] adapted to children (allowing shorter headache duration of 2 to 72 h, and bilateral instead of unilateral headache)History of migraine for at least 3 monthsAt least 3 headache days in the last 3 monthsMigraine prophylactic medication (beta-blocker, amitriptyline, topiramate) allowed if kept constant for the duration of the study

Exclusion criteria are:
Mental retardation (IQ < 70)Severe somatic or psychological, acute or chronic disease except headacheFamiliar hemiplegic migraine (genetically confirmed)Children will be excluded after the baseline phase if less than 3 headache days were present during the 3 months baseline phase

### Sample size calculation

The primary outcome was defined as a difference in reduction of headache days between the baseline and the follow-up period of ≥2 headache days in 12 weeks. The significance level α was set at 0.05 and the power at 0.9. Power size calculation with these parameters shows that a sample of *n* = 279 in the intervention group A (pediatric practice) and *n* = 507 children in the intervention group B (interdisciplinary treatment in social pediatric centers) is needed. For the sample size calculation an intra-class correlation coefficient (ICC) of 0.1 was assumed.

The estimated number for recruitment is based on an analysis of the Barmer insurance database of 2017 [1]. Approximately *n* = 270,000 statuarily insured children at the age of 6 to 11 years are likely to obtain a diagnosis of a primary headache disorder. About 70% of these see a pediatrician for primary care. As approximately 20% of pediatricians in practice use the website “PädExpert”, which provides the electronic migraine checklist, inclusion and exclusion criteria and access to the study platform, we calculated that *n* = 28,350 children per year are available for screening of migraine at the pediatric practices. We estimate that of these, 17.5% in fact receive a migraine diagnosis, resulting in *n* = 4961 children.

Germany was divided in 77 regions according to the postal codes, in a way that every postal code region contained at least one social pediatric center. The postal code regions were then randomized at a 2:1 ratio to intervention B and to intervention A regions. We estimated that in 75% of the intervention B regions at least one social pediatric center would be willing to participate in the study. We assumed that up to 20% of children will be excluded after the baseline phase or drop out later in the study: 1) because of more than 33% of missing data in the electronic headache diary during the baseline phase or 2) because of less than three documented headache days during the 3 months baseline or 3) because of more than 66% of missing data in the electronic headache diary during the follow-up period or 4) because they are lost to follow-up.

As shown in the flow chart (Fig. 1) the actual percentage of regions where at least one social pediatric center participated (intervention group B) was 73% (only slightly lower than estimated). Because of an assumed further drop out of 20% after recruitment, the numbers expected were *n* = 1931 and *n* = 1323 for the intervention B (social pediatric centers) and intervention A (pediatric practice) group respectively. These numbers exceed the required numbers as estimated in the power calculation. We chose a broad safety margin because of uncertainties related to the COVID-19 pandemic.

**Fig. 1 Fig1:**
[figure not shown]
Flow chart of the expected number of children with migraine treated by the interdisciplinary multimodal intervention in the social pediatric centers (intervention group B) and in the pediatric practice (intervention group A)

### Study design

#### Overview (Fig. 2)

As described above, the study compares the pediatric practice treatment (intervention group A) and the interdisciplinary multimodal treatment (intervention group B). The timeline is illustrated in Fig. 2.

**Fig. 2 Fig2:**
[figure not shown]
Study design, timelines and data acquisition

In both groups, children are diagnosed with migraine by their pediatrician in practice, included in the study and, if they have at least 3 days of headache in the baseline phase (week − 12 to 0), go on to the intervention phase (week 0–12). The intervention phase includes treatment at the pediatric practice for both groups, and treatment at the social pediatric center only for the interdisciplinary multimodal group (intervention group B). There, children are treated with the structured multimodal interdisciplinary intervention “moma” as described below. After the intervention the follow-up (week 12 to 24) is performed by the treating pediatrician in practice again.

Every participant has four study visits at the pediatric practice at time points − 12, 0, 12 and 24 weeks. The interdisciplinary multimodal intervention group has three additional study (intervention) visits at the social pediatric centers.

At the first visit, the moma web application generates a hashcode for pseudonymization of the patient, which is given to the parents by the pediatrician. The parents use the hashcode to log into the “moma App”, in which they document headache frequency, intensity and acute headache medication of their child on a daily basis.

#### Interdisciplinary multimodal intervention

The elements of the presented structured multidisciplinary intervention for children at the age of 6 to 11 years “moma” include:
pediatric elements such as exclusion of secondary causes and comorbidities by neurological examination and blood tests, and counselling regarding the bio-psycho-social model of pain,physiotherapeutic elements such as examination of myofascial trigger points in the neck and shoulder muscles, education about the association of muscle tenderness and migraine and about individual exercise and self-administered stretching measures,psychological elements such as evaluation of psychosocial circumstances, relevant psychological and behavioral factors for migraine, introduction of relaxation techniques and individual counselling to address the identified factors and improve self-efficacy.

The pathophysiological rationale for choosing these therapeutic elements is as follows:

According to epidemiological data, 45 to 85% of German adolescents with migraine (depending on migraine frequency) also suffer from muscle pain of neck or shoulders [9]. The pathophysiological explanation for this association is the concept of the trigemino-cervical complex (TCC) with its convergence of nociceptive afferents from cervical muscles to the caudal trigeminal nuclei [12]. As invasive or drug treatment is often not successful in young children, one focus of the presented intervention is on the cervical muscles as the easily accessible peripheral input of TCC [10]. With physiotherapeutic treatment of the muscle, including self-massage and stretching, the tenderness of the muscles is reduced which in our clinical experience leads to a decrease of headache frequency and/or intensity.

In addition, progressive muscle relaxation, which was shown to be effective in adults with migraine [13] was adapted for young children and is integrated in the psychological module of the presented intervention. Psychologists also screen for psychological stress and psychiatric comorbidities which are more frequent in patients with migraine compared to healthy persons [14]. The treated children are asked to draw their headache to visualize individual symptoms of migraine (Fig. 3) [15].

**Fig. 3 Fig3:**
[figure not shown]
Drawing of his headache by a 9-year-old child

#### Measures

All outcome parameters are assessed via the dedicated smartphone application ‘moma app’, which is filled in by the parents over the 9 months study duration (Fig. 2).

The app contains the following features:
Headache diary (based on established diaries [16, 17]) including a daily reminder function (missed entries days can be catched up within 2 weeks), with daily assessment of the following itemsPresence of headache (yes/no)Headache intensity (numeric rating scale 0–10 presented as a slider)Headache duration (slider from 0 to 24 h)Missed school (yes/no)Inabilty to perform leisure activities (yes/no)Use of headache medication (yes/no, tool for recording medication and dose)2.Questionnaires are presented within the app at the start and end of the baseline (weeks − 12 and 0), at the end of the intervention (week 12) and at the end of the follow-up (week 24). The following questionnaires are used:PedMIDAS (Pediatric Migraine Disability assessment score) [18]KINDL [19] (German tool for assessing pediatric quality of life).3.At the time points used for the questionnaires, the smartphone app also asks fortypical triggers of headache in the last 3 months (within the categories: school stress, family problems, conflicts with friends, noise, sport, inactivity, weather, lack of sleep, drinks containing caffeine, reduced fluid intake, high use of electronic media, infection, others)headache prophylactic measures taken in the last 3 months (within the categories: physiotherapy, trigger point therapy, osteopathy, acupuncture, homeopathy, alternative practitioner, naturopathy, peppermint oil, magnesium, vitamin D, medication, others)

Additionally to the ‘moma App’, pediatricians in practice and social pediatric centers use the ‘moma website’ (www.moma-migraine.de) [1] to document the individual clinical presentation and characteristics of the child, for example individual migraine symptoms, important aspects of the medical history, results of the neurological examination, psychosocial factors and the therapeutic recommendations given to the family. Furthermore, they estimate the complexity of the disease for each child using the ‘moma complexity signature’, which has been developed by our group specifically for this study based on the bio-psycho-social model (see Fig. 3 for time points of data acquisition).

### Outcome parameters

All outcome parameters are assessed via the parents’ entries in the ‘moma App’. For all outcome parameters, the difference from baseline to follow-up is measured and compared between the two groups.

The primary outcome parameter is the number of headache days per 12 weeks (84 days). Our hypothesis is that the reduction of headache days from baseline to follow-up will be at least 2 days larger for the group with interdisciplinary multimodal intervention in social pediatric centers (intervention group B) compared to the group with basic treatment in pediatric practices (intervention group A).

Secondary outcomes are:
Number of responders, defined as patients with a reduction of more than 50% of headache days per 12 weeks from baseline to follow-up;Headache intensity (averaged over headache days per 12 weeks);Number of days missed at school due to headache per 12 weeks;Number of days with cancelling of leisure activities due to headache per 12 weeks;Headache-related disability (PedMIDAS questionnaire) [18],assessed every 3 months;Quality of life (KINDL questionnaire, every 3 months) [19, 20];Number of days with intake of acute medication because of headache per 12 weeks.

### Data analysis plan

The statistical analysis is performed according to the CONSORT Statement recommendations for cluster-randomized trials [20]. In the intention-to-treat analysis all patients having started to use the ‘moma App’ are included. Primary endpoint is the number of headache days per 12 weeks (84 days).

Two forms of analysis are performed:
Intention-to-treat analysis (“Full Analysis Set”)

All patients who started to use the electronic headache diary (moma app) and fulfill the baseline criteria (see below) are included in the intention-to-treat analysis. Patients who have less than three headache days during the 12 weeks of baseline or from whom less than 33% of the days of the headache diary are filled in during baseline are excluded and are not part of the intention-to-treat analysis.
2.On-treatment analysis (“per protocol set“)

Patients who additionally completed all 4 study visits at the pediatric practices and (only in the intervention group) the three visits at the social pediatric centers and provided electronic headache diary data with less than 33% of the days missing during the intervention and follow-up phase are included in the per protocol analysis.

For headache diary data, missing data are treated as follows. If less than 33% of the days are missing, the missing data is replaced by the mean values of the existing data. If 33 to 66% of the headache diary data is missing, a modified last observation carried forward (LOCF) approach will be performed for the intention to treat analysis. To this end, missing days are replaced by the mean values of the the last 3-month period that has less than 33% missing data. If more than 66% of the data of the headache diary data is missing, a simple LOCF principle will be applied. For this, the data of the entire 3-month period will be replaced by the mean value of the last 3-month period with less than 33% missing data.

If one or more items of the PedMIDAS (6 items) is missing, the scale will be excluded from statistical analysis of this patient at this time point because it does not retain sufficient clinical informative value.

The KINDL questionnaire (4 subscales with 4 items each) allows one missing item per subscale which is replaced by the mean value of the other items of the subscale [19, 20].

For the primary end point (number of headache days per 12 weeks) a mixed linear regression model is performed with the difference of headache days per 12 weeks from baseline to follow-up as dependent variable, the intervention in a social pediatric center (yes/no) as independent variable and random effects for the different social pediatric centers. Age, sex and headache frequency per 12 weeks at baseline are included as possible confounders. Quality of life (KINDL) and migraine related disability (PedMIDAS) at baseline are possible effect modifying elements and therefore integrated in the model as interaction effects. The significance level α is set at < 0.05. The same model is used for analysis of the secondary outcome parameters.

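### The baseline diary threshold differs between the sample size section and the intention-to-treat definition, and the looser version admits children whose baseline count the imputation rules cannot produce

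*Protocol article*

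**What the plan says.** Two sections of the protocol article set a completeness threshold for the baseline diary.

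- **Sample size calculation.** The authors write: "We assumed that up to 20% of children will be excluded after the baseline phase or drop out later in the study". The first of the four listed reasons is "because of more than 33% of missing data in the electronic headache diary during the baseline phase".
- **Data analysis plan, intention-to-treat analysis (Full Analysis Set).** Apart from children with fewer than three baseline headache days, patients "from whom less than 33% of the days of the headache diary are filled in during baseline are excluded".

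The same Data analysis plan handles missing diary days in three bands:

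- Below 33% missing, the child's own data from that period are used: "If less than 33% of the days are missing, the missing data is replaced by the mean values of the existing data".
- From 33 to 66% missing, the missing days take the mean of the "last 3-month period that has less than 33% missing data" (a modified last observation carried forward, LOCF).
- Above 66% missing, the whole period is replaced from the same kind of donor period (simple LOCF).

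The Study design section places baseline at weeks −12 to 0, which makes it the first diary period. Each period has 84 days (Outcome parameters).

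**The concern.** The same 33% is attached to missing days in one section and to filled-in days in the other. The required completeness is therefore about two thirds in the first and one third in the second. A programmer who follows the Data analysis plan literally builds a different primary population from the one assumed in planning.

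The looser version also conflicts with the imputation rules in its own section. It admits children whose baseline is too sparse for the within-period mean, and the two remaining rules need a period that does not exist for baseline.

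Four quantities depend on the baseline count:

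- the dependent variable of the primary model (change from baseline to follow-up);
- the baseline headache frequency covariate in that model;
- the responder endpoint (a reduction of more than half from baseline);
- the exclusion of children with fewer than three baseline headache days. For this exclusion the Sample size calculation section speaks of documented headache days and the Data analysis plan only of headache days. With a sparse diary it is thus open whether imputed days count.

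A child with a sparse baseline also lacks a baseline donor if the intervention and follow-up diaries are both sparse.

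**Working it through.** There is no stated figure to reproduce. The check applies each written rule to every possible number of filled baseline days, *f* = 0 to 84, with missing share = (84 − *f*)/84.

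**Step 1: minimum completeness under each rule**

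- Sample size calculation: excluded if (84 − *f*)/84 > 0.33. At *f* = 57, 27/84 = 32.1%, kept. At *f* = 56, 28/84 = 33.3%, excluded. Minimum: 57 days.
- Data analysis plan: excluded if *f*/84 < 0.33. At *f* = 28, 28/84 = 33.3%, kept. At *f* = 27, 27/84 = 32.1%, excluded. Minimum: 28 days.

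**Step 2: the disputed range**

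Children with *f* = 28 to 56 (33.3% to 66.7% missing) are admitted by the Data analysis plan and excluded by the sample size section. That is 29 of the possible day counts.

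**Step 3: which imputation band applies to them**

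| Filled days | Missing share | Band | Source of values |
|---|---|---|---|
| 57 to 84 | 0 to 32.1% | below 33% | own baseline days |
| 29 to 56 | 33.3 to 65.5% | 33 to 66% (modified LOCF) | earlier period |
| 28 | 66.7% | above 66% (simple LOCF) | earlier period |

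No day count from 28 to 56 falls in the own-data band. As an example, a child with 40 filled days has 40/84 = 47.6% filled and is admitted by the Data analysis plan. The missing share is 44/84 = 52.4%, so the modified LOCF rule applies and finds no donor.

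**Step 4: effect of the stricter rule**

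With at least 57 filled days required, the largest missing share is 32.1%. Every admitted child then falls in the own-data band, and no baseline needs an earlier period.

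**Sensitivity to reading 33% as exactly one third**

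The sample size minimum becomes 56 days (28/84 is not more than one third), and the Data analysis plan minimum stays at 28. The conclusion is unchanged. The child with exactly 56 days would pass both rules and still miss the own-data band, which requires less than one third missing. For that reason the exclusion is better worded as 33% or more missing.

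**The case against.** The strongest reply is that the sample size section does not define the analysis set. It lists planning assumptions about losses and does not use the term intention-to-treat. Its list does not map one-to-one onto the analysis set either: it counts children with more than 66% missing at follow-up as lost, while the Data analysis plan keeps them through simple LOCF. This has force. It moves the weight of the point to the conflict inside the Data analysis plan, between whom it admits and whom it can impute, and that conflict stands without the sample size section.

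One could also read the donor as any well-filled period, including a later one. That would put values from after the start of the intervention into baseline, which is not carrying forward, and the text does not say it.

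Several stronger readings are tempting but not supported:

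- *The two rules run in opposite directions.* Both exclude sparse diaries. They differ in the completeness they require.
- *There are three conflicting definitions.* The section does open with "In the intention-to-treat analysis all patients having started to use the ‘moma App’ are included", but it then narrows the set to children who meet the baseline criteria. The opening is a loose summary.
- *The per-protocol set needs its own baseline limit.* That set is defined by additional requirements on top of the intention-to-treat criteria, so it inherits whatever baseline rule is fixed there.
- *A known number of children is affected.* The document gives no distribution of diary completeness. An assumed share of 5 to 15% of the 786 required children (279 + 507) would be 39 to 118, but nothing supports that share. The app's daily reminder and two-week catch-up work against missing days. The expected numbers after drop-out (1931 + 1323 = 3254) also far exceed the 786.
- *Sparse baselines would be undercounted by several days.* That assumes missing days are left blank, which the plan never prescribes. One child's error is also not comparable with the two-day difference between group means.
- *The choice will be made after data are seen.* The statistical analysis plan is not shown and may settle the rule. The protocol article leaves it open.

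**Conclusion.** The point holds as a defect in the written rules. The two sections set different baseline completeness thresholds (57 versus 28 of 84 days). Under the looser one, the baseline is undefined for every admitted child with 28 to 56 filled days. It must be fixed, because it determines membership of the primary population and the baseline value of its members, and the repair is cheap.

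The result rests on two readings: that 33% applies to the 84-day period, and that the donor period precedes the one being filled. The size of the effect on the trial result cannot be stated, since neither the number of such children nor their distribution between groups can be derived from the document. The imputation bands work at baseline only with the stricter threshold, which suggests that filled in was written where missing was meant. That is an inference about intent, and the text should not be left to depend on it.

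**What to change.** Use one baseline completeness rule in both sections, fixed before outcome data are examined by group.

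- **Simplest option.** Change the intention-to-treat definition so that children with 33% or more of baseline diary days missing are excluded, and word the sample size section the same way. All admitted baselines then fall under the existing within-period mean rule.
- **Alternative, if sparser baselines are to be kept.** State that the baseline count is always prorated to 84 days from the child's own documented baseline days, and that both LOCF rules apply only to later periods. Correct the sample size section to match.

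In either case, align the opening summary sentence of the Data analysis plan with the definition, and say whether the three-headache-day criterion uses documented days. The per-protocol set then follows without a separate limit.

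The cost is a wording change. The stricter option loses some children with sparse diaries, but that loss is already one of the four reasons within the 20% allowance. The alternative keeps them at the price of less precise baseline counts, resting on as few as 28 documented days.

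### The per-protocol set inherits a baseline diary limit that allows 56 of 84 days to be missing, twice what it allows in later phases and with no workable missing-data rule

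*Protocol article*

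**What the plan says.** The Data analysis plan of the Protocol article defines two analysis sets. The full analysis set takes children who started the app, had at least three headache days at baseline and met a diary minimum: those "from whom less than 33% of the days of the headache diary are filled in during baseline are excluded". The per-protocol set is nested within it. It holds "Patients who additionally completed all 4 study visits at the pediatric practices", in the interdisciplinary group also the three center visits, who in addition "provided electronic headache diary data with less than 33% of the days missing during the intervention and follow-up phase".

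The Sample size calculation section gives a different baseline diary limit. Among its reasons for exclusion or drop-out is "because of more than 33% of missing data in the electronic headache diary during the baseline phase".

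The primary model takes "the difference of headache days per 12 weeks from baseline to follow-up as dependent variable", with baseline headache frequency as an adjustment variable. The Outcome parameters section applies the same contrast throughout: "For all outcome parameters, the difference from baseline to follow-up is measured and compared between the two groups".

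Missing diary days are handled in three bands. In the lowest, "If less than 33% of the days are missing, the missing data is replaced by the mean values of the existing data". From 33 to 66% missing, the gaps are filled with the mean of the most recent 3-month period that has less than 33% missing; this band is written for the intention-to-treat analysis. Above 66%, the whole period is replaced by the mean of such a period.

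**The concern.** A per-protocol set is normally expected to hold the well-documented children. Here it applies a strict diary limit to the intervention and follow-up phases and a much weaker one to baseline, although baseline is half of the change score and enters the model again as a covariate. A child can thus count as per protocol with two-thirds of the baseline diary empty.

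Two things are at stake. Two analysts following the text could build different per-protocol sets, depending on which section they take the baseline limit from. And for a child admitted under the weaker limit, the article gives no usable way to obtain the baseline count, so the change score would depend on an unplanned decision made at analysis.

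**Working it through.** The check concerns day counts and the fit between rules. The article's sample sizes (279 and 507) do not bear on it, and they cannot be reproduced because no standard deviation or cluster size is stated.

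**Inputs.** Phase length is 84 days (Outcome parameters). The diary limits and missing-data bands come from the Data analysis plan, and the alternative baseline limit from the Sample size calculation.

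**Step 1: limits in days.** 33% of 84 is 0.33 × 84 = 27.72 days.

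| Rule | Condition to stay in | Fewest days filled | Most days missing |
|---|---|---|---|
| Baseline, Data analysis plan | filled ≥ 27.72 | 28 | 84 − 28 = 56 (66.7%) |
| Baseline, Sample size calculation | missing ≤ 27.72 | 57 | 27 (32.1%) |
| Per-protocol limit, later phases, read phase by phase | missing < 27.72 | 57 | 27 (32.1%) |

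In whole days, the Sample size limit and the per-protocol limit coincide. The Data analysis plan's baseline limit allows about twice as many missing days (56/27 = 2.1).

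**Step 2: which missing-data rule serves a sparse baseline?**
- 0 to 27 days missing (up to 32.1%): the mean of the period's own data. This works.
- 28 to 55 missing (33.3 to 65.5%): modified carry-forward. It needs an earlier 3-month period with less than 33% missing. The diary starts with the baseline phase at week −12, so there is none. The rule is also written for the intention-to-treat analysis only.
- 56 missing (66.7%): simple carry-forward, which needs the same non-existent earlier period.

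For 28 to 56 missing baseline days, then, a child may be in the per-protocol set but has no baseline count under the stated rules, and so neither a change score nor a covariate value.

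**Step 3: size, for illustration only.** Suppose an analyst scaled up the observed days. The article does not prescribe this at 33% or more missing. With days missing at random, *n* filled days and *p* the headache-day proportion, the error SD of the scaled count is 84 × √[*p*(1 − *p*)/*n* × (84 − *n*)/83].
- 8 headache days in 84 (assumed): 3.83 days at *n* = 28; 1.86 days at *n* = 57.
- 12 headache days in 84 (assumed): 4.56 and 2.22 days.

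These are errors for one child, whereas the 2-day target is a difference between group means. To see the group effect, assume that 10% of per-protocol children sit at the 28-day extreme rather than at 57 days, with 8 headache days each. The average variance rises by 0.10 × (3.83² − 1.86²) = 0.10 × (14.7 − 3.5) = 1.1. The outcome SD is not stated. The planned sample sizes with two-sided α 0.05, power 0.9 and a 2-day difference imply about 8.3 without clustering, or 6.0 with an assumed cluster size of 10 at the stated ICC of 0.1. The corresponding variances are 69 and 36, so the increase is 1.1/69 = 1.6% to 1.1/36 = 3.1%. Under these assumptions the loss of precision is small; the undefined handling is the main problem.

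**The case against.** The strongest reply is that baseline is already screened. The Sample size calculation excludes children with more than 33% of the baseline diary missing, and the carry-forward rules make sense only on that footing. The weaker wording in the Data analysis plan may be a slip between days filled and days missing. If so, a per-protocol sentence that names only the two later phases is coherent, since baseline has been dealt with. This is a plausible account of what was intended, and it is why the finding is conditional. But the weaker limit stands in the section that defines the analysis sets, and the article does not say which limit governs.

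A reader might go further and infer that baseline is not checked at all in the per-protocol set. The text does not support that. The word *additionally* carries over the full-analysis-set criteria, so a baseline limit exists; it is only much weaker.

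A reader might also infer that the intervention-phase diary condition is wrong because those days do not enter the endpoint. It does remove a child with complete baseline and follow-up diaries and 28 missing days in weeks 0 to 12. But daily diary entry over the whole study is a protocol procedure, and a per-protocol set may require adherence to it. Such children stay in the intention-to-treat analysis if they meet its baseline criteria.

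Finally, an error of 3.8 days for one child must not be set against the 2-day target as if it were a bias. It rests on an estimator that the article does not prescribe, on randomly missing days and on the extreme permitted case.

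**Conclusion.** The point holds in a limited form. Read literally, the Data analysis plan lets a per-protocol child have up to 56 of 84 baseline days missing, against 27 in each later phase, and leaves baselines with 28 to 56 missing days without a workable missing-data rule. This rests on the baseline limit in that section being the governing one and on the 33% limit being applied phase by phase. If the limit in the Sample size calculation governs, the baseline gap closes and only the contradiction between the two sections remains.

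The article does not say how many children would be affected, so the effect on the per-protocol estimate cannot be sized. The illustration suggests that it would be modest. The per-protocol sentence itself does not affect the intention-to-treat set.

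**What to change.** Reconcile the baseline diary limit between the Sample size calculation and the Data analysis plan. Then state in the per-protocol criterion that less than 33% of diary days may be missing in the baseline phase as well as in the follow-up phase. This is one sentence, needs no new data, and agrees with the Sample size section and with the missing-data rules. The cost is that a few children with sparse baselines leave the per-protocol set.

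If the weaker limit is deliberately kept for the full analysis set, that set needs its own rule for baselines with 28 to 56 missing days, because carry-forward cannot supply one.

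The intervention-phase diary requirement can stay. If it does, a line giving its purpose as diary adherence would help, and a sensitivity analysis without it is optional.
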